In addition, if no data points are missing, the smart phone app should generate an approximate maximum of 560 measurements on participants’ mood [16 persons x 5 times per day x 7 days]. Within-day and between-day variations, as the temporal manipulation of process changes take place, will be of primary interest. The substantial number of data points will also provide a basis for modelling the data through repeated measure mixed method design, which will provide an average scenario of mood stability/variation after controlling for auto correlation that arise from repeated measures and controlling for time related variations. It is important to note that due to the small number of participants, generalizability from mixed model will be limited. Rather, the mixed method model is applied here to capture the real trend from repeated measures after controlling for auto correlations.

In addition, this study will generate rich data at the level of individual participants, and this will be explored using trend analysis to identify patterns of change across time, and possible predictors of therapy attrition and effect. However when it comes to reporting these data, care will be taken to balance the need for communicating potentially important findings with the need to protect participant anonymity, given that the report may be accessed by their peers in the group.

With regard to qualitative data written notes will be made of answers to interviews. These notes will be checked back with participants to ensure that they represent his / her own words. Thematic analysis will be used to identify key themes in the transcripts. This will be done separately by two researchers for the first five scripts. The themes identified by the two will be compared and a set of key emerging themes agreed. Additional transcripts will be coded by one researcher and contemporaneous notes made of the extent to which the existing themes are supported by the remaining transcripts, and of any new emergent themes. This work will be reviewed with the second researcher after a further 15 transcripts have been coded. The second researcher will compare the themes against the data and identify any that are redundant, inappropriate or have been missed. A final set of themes will be agreed by the two researchers.

Ethical Issues

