We have developed a protocol for group-based DBT training that draws upon theoretical and empirical work into basic processes in Bipolar Disorder to adapt standard DBT for this client group. The format of the group is designed to make this intervention feasible to deliver within outpatient primary or secondary mental health settings whilst allowing for individualisation and generalisation of skills through individual skills-coaching sessions and the use of a mobile phone application (Rizvi et al., 2011).

Study Aims and Hypotheses

The aim of this study is to formally evaluate group DBT skills training for individuals with ongoing bipolar mood instability (frequent mood swings that persist outside of – or instead of - full episodes of illness). This will provide information that can be used to further refine the content and delivery of the intervention and inform the design of a pilot randomised controlled trial of the intervention.

Evaluation will primarily focus upon:

1. The feasibility and acceptability to participants and referring clinicians of i) the content of the intervention; ii) the delivery of the intervention (in terms of group and individual components, the “open” nature of the group element, and the use of experience sampling to support therapy).
2. Testing key outcome variables observed in participants in the group.
3. Evidence for mechanisms of change within participants in the group.

Hypotheses:

1. The intervention will be both feasible and acceptable to participants, clinicians and refers as measured through uptake and adherence rates, and qualitative feedback.
2. Between the baseline assessment and the end of the group participants will show i) a trend of decreasing levels of depressive and manic symptoms; ii) decreases in variability of symptoms and day-to-day mood; iii) increases in quality of life and sense of personal recovery.
3. The above changes will be i) associated with; ii) preceded by increases in mindfulness and group fit, and decreases in behavioural avoidance, positive and negative urgency, impulsivity and problematic beliefs about extreme mood states.

Experimental Design and Methods

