**Method**

*Participants*

Participants will be up to 16 individuals recruited through the Mental Health Assessment Team in the Exeter and East Devon area, and in the Mid Devon area if necessary.

In addition we will invite at least four members of staff from referring services to provide data on the acceptability of the Thrive programme.

Inclusion criteria for patient participants are: i) aged 18 or over; i) meets DSM-V criteria for Bipolar Spectrum Disorder; iii) current bipolar mood instability (over the past two years numerous periods with hypomanic symptoms that do not meet criteria for a hypomanic episode and numerous periods with depressive symptoms that do not meet criteria for a depressive episode, continuing into the past month); iv) client wishes to engage in psychological therapy that focusses primarily on ongoing mood instability and its consequences.

Exclusion criteria are: i) current substance dependence disorder; ii) currently receiving other psychological therapy; iii) the patient is currently actively suicidal; iv) presenting difficulties that are characteristic of Borderline Personality Disorder rather than Bipolar Disorder and that would be an early treatment target in standard DBT (frequent and serious deliberate self-harm, marked disturbance in ability to form or maintain interpersonal relationships); v) presence of another area of difficulty that the therapist and client believe should be the primary focus of intervention (for example panic disorder with agoraphobia, Post Traumatic Stress Disorder); vi) the information available suggests that the person may present a significant risk to other group members (such as aggression, likelihood of carrying out sexual or other exploitation); vii) the person lacks capacity to consent to treatment or research participation; viii) currently experiencing an episode of mania.

Inclusion criteria for staff participants are: i) mental health professional working within a service that can refer patients to the study.

*Materials*

Structured Clinical Interview for DSM-IV (SCID V: First, Williams, Karg & Spitzer, 2015): This is a clinician rated semi-structured interview for ascertaining diagnostic status according to the Diagnostic and Statistical Manual for Mental Disorders (DSM-IV: American Psychiatric Association, 2000) and is the gold standard for obtaining a diagnosis for research purposes.

*Outcome Measures*

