Bech Mania Rating Scale (BMRS: Bech, Rafaelson, Kramp & Bolwig, 1978): An 11 item observer rated instrument, with higher scores corresponding to higher levels of hypomania or mania. This scale has been shown to have good internal consistency and construct validity.

Altman Scale for Rating Mania (ASRM: Altman, Hedeker, Peterson & Davis, 1997): A five item self-report measure of current manic symptom level that has been validated in patient populations .

The Bipolar Disorder Recovery Questionnaire (BDRQ: Jones, Mulligan, Higginson, Dunn & Morrison, 2013): A 36 item self-report measure that has been developed to measure personal recovery in people with Bipolar Disorder, as distinct from symptomatic or medical recovery. The BDRQ has been found to have adequate internal consistency and convergent validity.

The Brief Quality of Life in Bipolar Disorder scale (QoL.BD: Michalak & Murray, 2010): This is a 12 item self-report measure of quality of life that has been specifically designed for and validated with individuals with Bipolar Disorder.

Acceptability Questionnaires: Before starting the programme, participants will be asked about the extent to which they find it acceptable, and their general views on being offered a group treatment, as will referring clinicians. After completing the group participants and clinicians will be asked about their experience of the programme. The questionnaires contain both qualitative and quantitative elements, and includes questions about the smartphone app, based on a measure used in a previous published study (Rizvi et al., 2011).

Experience Sampling Measure (ESM):

Participants in the group will make use of a mobile phone application (“app”) which has been purpose designed by the experimenter for use in this study. This application alerts the individual 5 times per day over a period of 7 days. On each occasion the user is asked to rate his / her mood on a scale of -10 to +10. They are also asked if they have done anything since the last alert deliberately to regulate their mood, and if so, the extent to which this was helpful. This app will be used at the start and the end of the study to measure within and between day fluctuations in mood, and use of helpful coping responses.

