The intervention consists of 16 sessions of group skills training based upon DBT, supported by individual meetings of up to 30 minutes that occur approximately monthly for each person, immediately following the end of each group session. The original DBT protocol and materials have been adapted for use with individuals with Bipolar Disorder by the applicants, and have been used clinically within two previous groups. Feedback from clinicians and patients involved in these groups has been used to iteratively refine the protocol and materials. The current version of the group follows a modular format: participants complete these modules in the following order (mindfulness, emotion regulation, mindfulness, distress tolerance, mindfulness, interpersonal effectiveness, consolidation), however if a participant leaves the group early, another participant can take his / her place at the start of the next module. This helps to maximise the number of people that can take part in the group. We will run two cycles of the entire 16 week group, to allow us to adequately test the feasibility of an open group design (whereby some participants may have started midway through the first cycle of the group, thus require the opportunity to complete the modules they missed, during a second cycle). No new participants will be able to join the group later than the start of the “emotion regulation” module of the second cycle, to ensure that all participants have the opportunity to be exposed to all modules. The group will finish after the end of the second cycle, or after the last participant has completed all modules, whichever is sooner.

After the end of the first group, “reunions” will be held every 3 months until all participants in both groups have had the opportunity to attend at least one reunion. All participants who have finished treatment will be invited to these, and sessions will focus upon celebrating practice done by participants and gains made, and by supporting participants with recently difficulties through group consideration of how skills learned could be applied.

*Procedure*

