Patient participants will be identified by staff members in the xxxxxxx Mental Health Assessment Team (with the xxxxxxx Assessment Team being a second possible recruitment source if necessary) on receipt of referrals of individuals with Bipolar Disorder. If necessary we will also recruit from Recovery services (secondary mental health teams) in Exeter. Participants likely to meet study criteria will be informed about the study by the assessing staff member during a routine assessment appointment (given Participant Information Sheet). If necessary the patient and / or staff member can liaise with the research team to address questions about the study and study eligibility that arise at this stage. Patients expressing an interest in the study will then be referred to the AccEPT service, which hosts the project. Once referred, potential participants will be contacted to explain the study, have an opportunity to answer questions, and arrange an assessment appointment if they wish to proceed. At the assessment appointment the researcher will explain the study further, address questions and take informed consent. Following this the researcher will ascertain whether the participant meets study inclusion / exclusion criteria (the SCID will be used to investigate criteria pertaining to diagnosis). If the participant is not eligible for the study this will be explained and the participant referred onwards as appropriate. If the participant is eligible he / she will be invited to complete the “outcome” and “process” measures listed above, in addition to the standard assessment measures used within the AccEPT service. This can be done in the University or at home, in accordance with the participant’s preference. The participant will also be asked to complete the ESM recording period for a week prior to starting the group. He / she will be instructed in the use of the app at the end of the assessment session.

Participants will then undertake treatment as per the usual procedures at the AccEPT service; this involves completing measures of symptoms (ASRM and BDI-II) at each session. To this we will add the single item measure of group fit, and a single visual analogue scale of mood that day (from -10 to +10).

In addition participants will complete the following measures half way through the group cycle: UPPS-P, KIMS, BADS, HAPPI, IIP-32.

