At the end of treatment participants will complete the standard set of “exit” questionnaires for the AccEPT service plus the outcome and process measures and SCID mood disorders section for the period since initial assessment, and will return for an individual meeting (standard practice).

Participants will be followed up six months after the end of treatment when they will complete the BDI-II, ASRM, QoL.BD, BDRQ, acceptability and group fit questionnaires, as well as the SCID mood disorders section for the past six months.

Staff participants will be identified by the CI informing the teams concerned at a team meeting. Information sheets and consent forms will be distributed. Staff will be able to opt to complete either an anonymous questionnaire, an interview, or both. Questionnaires will be left at the team base for staff members to complete, and a researcher will return at a later date to collect the completed anonymous forms. For staff wishing to take part in the interview, they will be asked to contact the research team to discuss further. If he / she remains interested an appointment will be arranged either in person (in the staff member’s place of work, or at the University of Exeter) or over the telephone. This will take around 20 minutes. Staff will be asked to complete these on two occasions: before the first participant starts the Thrive programme, and after the final patient completes.

*Statistical Analysis*

In order to assess acceptability and feasibility descriptive statistics will be used to represent participant uptake and retention across the study. In addition, acceptability interview data will be presented in terms of descriptive statistics, and qualitative data will be subjected to thematic analysis.

Mean change in questionnaire scores will be assessed through presentation of descriptive statistics and use of non-parametric tests (paired sample Wilcoxon Signed Rank Test).

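### The protocol gives no route to early leavers' views of the programme, so post-programme acceptability, one part of Hypothesis 1, is open to favourable bias

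*Protocol*

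**What the plan says.** The first item that the evaluation will focus on (Protocol, Study Aims and Hypotheses) is "The feasibility and acceptability to participants and referring clinicians of i) the content of the intervention; ii) the delivery of the intervention". Hypothesis 1 expects the intervention to be feasible and acceptable, "as measured through uptake and adherence rates, and qualitative feedback".

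Acceptability questionnaires are described under Outcome Measures. There is a pre-programme form: "Before starting the programme, participants will be asked about the extent to which they find it acceptable". There is also a later one: "After completing the group participants and clinicians will be asked about their experience of the programme". The Procedure section opens its end-of-treatment paragraph with "At the end of treatment participants will complete the standard set of" and adds the study's outcome and process measures to the clinic's exit forms. Since the acceptability questionnaires are listed among the outcome measures, they are collected then, and again six months after the end of treatment.

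The Intervention section foresees early leaving: "if a participant leaves the group early, another participant can take his / her place at the start of the next module". No section describes an exit questionnaire, interview or contact for a person who leaves in this way.

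On recruitment, assessing staff first tell likely candidates about the study. The Procedure section continues: "Patients expressing an interest in the study will then be referred to the AccEPT service". No count of the patients told is described, and the Statistical Analysis section reports uptake descriptively without naming its denominator.

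**The concern.** People who found the content, the group format or the app unacceptable are likely to be over-represented among those who leave. If the post-programme questionnaire reaches only those still present at the end, the views most useful for refining the intervention are the ones most easily lost. The open format is itself something the study sets out to evaluate, and leaving and refilling are part of that format. The Statistical Analysis section also plans to look for predictors of attrition, but no planned measure asks a leaver why they left.

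The results are meant to inform the design of a pilot randomised trial. A favourable acceptability figure could carry an unsuitable element into that trial. A later analysis plan could define a denominator, but it could not recover opinions that were never collected.

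**Working it through.** The protocol states no acceptability rate, attrition rate or threshold, so there is no figure of its own to reproduce. The check is a reading of the sections together, followed by an illustration on assumed values.

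**Reading**

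1. Outcome Measures ties the post-programme questions to completing the group.
2. Procedure ties the same measures to the end of treatment and to six months after it. It refers to participants generally, without restricting the measures to completers and without saying what happens for someone who stops early.
3. Intervention treats leaving early as distinct from completing the modules, and provides for replacement.
4. Taken together, a team following the text would have a clear instruction for completers and none for leavers.

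**Illustration for acceptability**

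Inputs:
- Starters: 16, the cap under Participants ("Participants will be up to 16 individuals recruited through the Mental Health Assessment Team"). Replacements are assumed to count within this number.
- Completers finding the programme acceptable, p_c: 90% (assumed).
- Leavers, d: 2, 4 or 8 (assumed).
- Leavers finding it acceptable, p_l: 0% to 90% (assumed), so leavers are taken to be no more favourable than completers.

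Formulae: all-starter rate = [(16 − d) × p_c + d × p_l] / 16, and overstatement = p_c − all-starter rate = (d/16) × (p_c − p_l).

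| Leavers | All-starter rate, p_l = 0% | All-starter rate, p_l = 90% | Overstatement |
|---|---|---|---|
| 2 | (14 × 0.9)/16 = 78.75% | 90% | 0 to 11 points |
| 4 | (12 × 0.9)/16 = 67.5% | 90% | 0 to 23 points (22.5 before rounding) |
| 8 | (8 × 0.9)/16 = 45% | 90% | 0 to 45 points |

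At an intermediate value, with 4 leavers and p_l = 50%, the all-starter rate is (10.8 + 2)/16 = 80%, an overstatement of 10 points.

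**Illustration for uptake (secondary)**

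If 16 enrol out of 20 who expressed interest, uptake is 16/20 = 80%. If 24, 32 or 48 patients had been told about the study, uptake against that number would be 16/24 = 67%, 16/32 = 50% or 16/48 = 33%. All counts except the 16 are assumptions. They show only that the choice of denominator matters.

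**The case against.** A reader might infer that the protocol restricts the post-programme questionnaire to completers. The text does not go that far. The sentence under Outcome Measures also covers clinicians, who do not complete a group, so it can be read as fixing a time point in contrast to the pre-programme form. The Procedure wording could include leavers. Where the authors mean finishers they can say so, as they do for the reunion invitations. This stands: the fault is an omission and an unclear instruction, and no stated exclusion can be shown.

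A reader might also infer that the first-listed aim is judged wholly on a favourable subset. The documents contradict this. Leavers contribute to pre-programme acceptability, to group fit at each session they attend, to adherence and retention, and to the exploration of attrition. Staff views add a further source. With 4 of 16 leaving, the retention figure of 12/16 = 75% would stand beside any acceptability figure, so readers would see the loss. This stands too and limits the point to one component. However, none of these sources records what a leaver thought of the programme overall after experiencing it, or why they left.

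A third tempting inference is that patients who decline at first approach are never counted in uptake. The protocol leaves the denominator undefined, which a statistical analysis plan may settle, and it does not say that assessing teams keep no count. Wanting this kind of therapy is also an inclusion criterion, so some decliners would be ineligible, and the number of patients told is one of several reasonable denominators.

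Finally, the questionnaires mix qualitative and quantitative items, and no binary acceptability endpoint or progression rule is specified. The percentages above therefore illustrate sensitivity and do not predict what will be reported.

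**Conclusion.** The point holds in a limited form. The protocol expects early leavers and replaces them, but makes no provision for learning their views of the programme. Post-programme acceptability is therefore liable to favourable bias. The size is unknown: on the assumed values it runs from 0 to 23 points with 4 leavers of 16, and up to 45 points with 8. The lower end is zero, reached if leavers judge the programme as completers do or if the team in practice gives leavers the form. The direction rests on the assumption that leavers are, on average, no more favourable than completers.

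This is a cheap improvement to one component of Hypothesis 1 and does not invalidate the aim. It belongs in the protocol because it concerns data collection. The uptake matter is secondary, being mainly missing detail.

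**What to change.** Amend the Acceptability Questionnaires paragraph under Outcome Measures, and the end-of-treatment and follow-up paragraphs under Procedure, so that the existing acceptability questionnaire or interview is offered to every participant who attended at least one session, at the point of leaving or finishing. Report the results against all starters, with leavers and non-responders shown separately.

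The cost is one call or posted form per leaver in a study of up to 16 people. Some leavers will not reply, but reported non-response is preferable to an unseen gap.

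As a secondary step, ask the assessing teams to keep an anonymous tally of patients told about the study, so that uptake can be reported against that number as well as against those referred. This needs only a tally sheet.

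### Questionnaire baselines are attached to the assessment step rather than to group entry, so any time between the two is counted as treatment change

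*Protocol*

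**What the plan says.** All references are to the Protocol.

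- **Eligibility and questionnaires (Method, Procedure).** At the assessment appointment consent is taken, then "Following this the researcher will ascertain whether the participant meets study inclusion / exclusion criteria". Next, "If the participant is eligible he / she will be invited to complete the" outcome and process measures. On place, "This can be done in the University or at home, in accordance with the participant’s preference". No date or window relative to group entry is given.
- **App recording (same section).** "The participant will also be asked to complete the ESM recording period for a week prior to starting the group". This is the only baseline instrument tied to entry.
- **Session measures (same section).** ASRM, BDI-II, the group fit item and a mood scale are completed at each session.
- **Entry (Method, Intervention).** If someone leaves early, "another participant can take his / her place at the start of the next module". The last permitted entry is the start of the emotion regulation module in the second cycle.
- **Interval tested (Study Aims and Hypotheses).** Hypothesis 2 begins "Between the baseline assessment and the end of the group participants will show". The exit SCID mood section likewise looks back to the initial assessment.
- **Test (Method, Statistical Analysis).** "Mean change in questionnaire scores will be assessed through presentation of descriptive statistics and use of non-parametric tests", namely the paired Wilcoxon signed-rank test.
- **Time-bound criteria (Method, Participants).** Several criteria describe a state at one moment, for example "currently experiencing an episode of mania", active suicidality, other therapy in progress, and instability continuing into the past month.

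**The concern.** The design has no control group, so a pre-post difference can be credited to the group only if it spans little besides treatment. The plan secures this for the app by fixing its recording to the pre-group week, but not for the questionnaires. A participant who waits after assessment contributes a questionnaire change covering waiting plus treatment and an app change covering treatment only. The two sets of results then describe different periods for the same person.

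Hypothesis 3 is touched as well. It asks whether change in the process scales precedes change in outcome, and for a person who waited, the change in those scales from baseline to mid-cycle includes untreated time.

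This is a matter of when data are collected. A pre-entry value that was never taken cannot be restored by a later analysis plan.

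A secondary point has the same cause: criteria worded for the present are checked once, at assessment, and the text does not say whether they are meant to hold then or at entry.

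**Working it through.** **The plan's own figure.** The protocol gives no figure on waiting time. Its one computed figure, 560 app measurements, reproduces (16 × 5 × 7 = 560) but does not bear on this point.

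**Step 1: which measures have a value near entry?**

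| Measure | Value near entry? |
|---|---|
| App mood ratings | Yes, week before the group |
| ASRM, BDI-II | Yes, at the first session, though not named as baseline |
| Group fit | Rated at each session |
| BMRS, QoL.BD, BDRQ | No |
| UPPS-P, KIMS, BADS, Brief-HAPPI, IIP-32 | No (next value is mid-cycle) |

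**Step 2: the longest wait the text allows.** Inputs are two 16-week cycles (32 weeks) and latest entry after the first mindfulness block of cycle 2. Block length *m* is not stated. I assume 1 to 4 weeks, with 16/7 = 2.3 weeks if the seven blocks were equal. I also assume weekly sessions, no gap between cycles, and a person assessed as the group opens.

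- Wait = 16 + *m*; share of the interval to the end of the group = (16 + *m*)/32.
- *m* = 1: 17/32 = 53%. *m* = 2.3: 18.3/32 = 57%. *m* = 4: 20/32 = 63%.

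This is an extreme case. For an assumed wait *w* before a full 16-week course the untreated share is *w*/(*w* + 16): 4/20 = 20%, 8/24 = 33%, 16/32 = 50%.

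**Step 3: from person to group mean.** Suppose, purely for illustration, a 0.5 SD excess at assessment that halves every 4 weeks. The loss per person is 0.5 × (1 − 0.5^(*w*/4)): 0.25 SD at 4 weeks and 0.44 SD at 12 weeks. If *k* of 16 wait, the group mean moves by *k*/16 of that. With *k* = 4 it is 0.06 to 0.11 SD.

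**Step 4: effect on the Wilcoxon test.** Simulation with n = 16, normal change scores, no treatment effect, two-sided 0.05 (assumed), and an assumed shift of 0.2 to 0.5 SD of the change score in those who waited. There were 5,000 runs per setting, with simulation error near √(0.05 × 0.95/5000) = 0.003.

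| Number who waited | Chance of p < 0.05 |
|---|---|
| No shift | about 0.04 to 0.05 |
| 4 of 16 | 0.05 to 0.07 |
| 8 of 16 | 0.06 to 0.13 |
| 16 of 16 | 0.10 to 0.43 |

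**Step 5: repeat burden.** Self-report items: UPPS-P 59 + BADS 25 + KIMS 39 + Brief-HAPPI 30 + IIP-32 32 + BDRQ 36 + QoL.BD 12 + ASRM 5 = 238, plus the 11-item observer-rated BMRS.

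**The case against.** The strongest reply is that the wait is nowhere stated. The Procedure reads naturally as one sequence: assessment, app instruction at the end of that session, the app week, then treatment. That fits a short gap. A vacancy is filled at the next module start, which may leave time to assess someone after the vacancy arises. A reader might infer a pool of assessed patients waiting for places; the protocol describes none. **This stands**: long waits are permitted, not planned.

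A reader might also infer that all the evidence of change is compromised. It is not. The session ASRM and BDI-II, the session mood rating and the app week give hypothesis 2 near-entry values for self-rated mania, depression and day-to-day mood. **This stands** and limits the point to the eight measures without such a value.

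It is tempting to say that patients are assessed at a peak and then settle. The documents do not show this. The research assessment follows a routine assessment and an onward referral, and inclusion requires instability over two years. The direction of any drift is therefore unknown, and moving the baseline would not remove natural course or regression to the mean from an uncontrolled trial. **This stands.**

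Finally, the study puts feasibility and acceptability first and is meant to inform a pilot randomised trial. That lowers the stakes, but paired tests of change are still planned, and the protocol already accepts the principle of a pre-entry baseline for the app.

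On eligibility, a reader might infer that excluded patients will enter the group. The text does not support that: risk, if detected, is handled under the service's established procedures, and symptoms are measured each session. What remains is only that the time point of the criteria is undefined.

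**Conclusion.** The point holds in a limited form. As written, the plan counts any time between assessment and entry as treatment change for BMRS, QoL.BD, BDRQ, UPPS-P, KIMS, BADS, Brief-HAPPI and IIP-32, and it sets no maximum wait or repeat baseline. Because the app recording week precedes the group and app instruction is given at assessment, a gap of about a week is built in for everyone. Anything longer depends on how recruitment runs.

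The size is unknown, since neither the wait nor the number affected is stated. Under the assumed shifts, the false-positive rate barely moves if 4 of 16 wait (0.05 to 0.07) and is material only if most do (up to 0.43 if all 16 wait with a 0.5 SD shift). The 53% to 63% untreated share is the limit of what the entry rule permits, not an expectation. The change is worth making because it is cheap and the missing values could not be recovered later. The eligibility point is secondary and is one of wording.

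**What to change.** 1. In Method, Procedure, have the baseline outcome and process measures completed in the same pre-group week as the app recording, or repeated then if they were completed well before entry.
2. In hypothesis 2, define baseline as this pre-entry set. Where no pre-entry repeat exists, use the first-session ASRM and BDI-II as baseline for those two scales.
3. Report the time from assessment to entry for each participant in summary form.
4. Reconcile the time-bound criteria under Participants with the single check described under Procedure by stating the time point to which they apply. No clinical rule is proposed here.

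**Cost.** For participants who have not yet completed the set, this is mainly rescheduling. Those who waited repeat up to 238 self-report items and the BMRS rating. BMRS is observer-rated, so it needs a contact with a rater, and the protocol's resources section gives the Chief Investigator little time. The burden falls only on those who waited, so it grows with the problem it corrects.
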